### Study design

The clinical study of the TINSA is a pragmatic pre−/post four-phase mixed methods study with non-randomised comparative groups, a convergent parallel design, and longitudinal follow-up at 3-months after hospital admission. The main quantitative element of the study incorporates descriptive and cross-sectional analytic components and measures designed to evaluate and compare four periods of time during which existing and new transdisciplinary stroke assessments are evaluated (see Fig. 1). Only the allied health stroke assessment component of the patient admission to the MHB ASU will be evaluated, and subsequent allied health input will continue as per usual care. Phase 1 (baseline, usual care) and Phase 2 (implementation of TINSA) will recruit participants experiencing symptoms of mild stroke or Transient Ischaemic Attack (TIA) and evaluate usual assessment compared to the novel TINSA (respectively). Between Phases 1 and 2, a 1-month transition phase will take place to allow staff to become familiar with the novel TINSA, complete competency training, and practice the new clinical process. Phase 3 (baseline, usual care) and Phase 4 (implementation of TINSA) will recruit participants experiencing moderate to severe stroke symptoms to evaluate usual assessment compared to the novel TINSA (respectively). Phases 3 and 4 will occur in parallel with Phase 2 and be time-limited (3 months/phase) due to time constraints on the ASU. Due to the nature of the clinical processes and staffing on the MHB ASU, neither randomisation nor blinding are feasible.

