### Outcome measures

A complete list of outcome measures is provided in Table 1.

**Table 1 Tab1:** List of outcome measures

Outcome	Measures
Time-efficiency	• Total time of allied health stroke assessments • Time from admission to enactment of social work referral • Time from admission to commencement of allied health intervention/rehabilitation • Occasions of face-to-face service with AHPs (occupational therapy, physiotherapy, speech pathology, social work) • Number of referrals to AHPs (occupational therapy, physiotherapy, speech pathology, social work) where no intervention or further assessment is indicated • Number of patients who received allied health assessment but had a negative stroke diagnosis on MRI • Time from admission to discharge from allied health (occupational therapy, physiotherapy, speech pathology) • Length of hospital stay
Cost savings	• Economic evaluation to determine difference in utilisation of hospital resources, such as bed space and AHP time
Quality of care (patient safety)	• Total number of adverse events during the hospital admission that may be related to allied health input (falls, extension of stroke, aspiration pneumonia, pressure injuries) • Missed allied health referrals (other than those due to a change in condition) • Failed discharge, defined as unplanned readmission within 30 days not related to a new episode of care
Quality of care (compliance to national stroke guidelines)	• Time from admission to allied health assessment (occupational therapy, physiotherapy, speech pathology) • Time from admission to commencement of allied health intervention (occupational therapy, physiotherapy, speech pathology) • Time from admission to mobility assessment • Time from admission to communication assessment
Utility of the novel TINSA	• Number of sections attempted/completed on the novel TINSA • Number of “stop and refer” prompts used on the novel TINSA • Number of allied health referrals identified from the novel TINSA
Patient and staff satisfaction	• Patient satisfaction survey • Staff satisfaction survey • Staff focus group
Staff trust and confidence	• Staff interprofessional trust surveys • Staff confidence surveys (pre/post competency training) • Staff building confidence surveys (monthly intervals)

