#### Retrospective medical record audit

A retrospective audit of patient medical records will collect data relating to time-efficiency (e.g., occasions of service), patient safety and adverse outcomes (e.g., number of patient falls), AHP compliance to national stroke guidelines (e.g., assessment completed within 48 hours of admission), and utility of the TINSA (e.g., number of sections completed). The audit of each participant’s medical record will occur at least 2 weeks after patient discharge, to allow sufficient time for the paper medical records to be scanned onto the hospital’s electronic record system (Verdi).

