
### Data management and monitoring

The Principal Investigator (AM) will be responsible for distribution and collection of surveys, medical record audits, completing the 3-month follow-up phone calls, and entering all data into a password-protected Excel worksheet. The Excel worksheet will be stored in a secure file and only the Principal Investigator will know the password. Data will be stored using numbers, where all categorical variables (e.g., discharge destination) will be assigned a numeric code. Once all participant data has been entered into the Excel worksheet and the study has closed, the data column containing the unique participant identifiers will be deleted, leaving only the data of interest for statistical analysis. Participant data will become unidentifiable at that point. Following analysis, the data will be deposited in an appropriate institutional data repository (The University of Queensland eSpace).

During the study period, the MHB ASU team will take on the role of the Data Monitoring and Safety Committee (DMSC). The DMSC will meet each fortnight to review study conduct and patient safety. The pre-specified review, stopping and discontinuation rules include if 1) data are collected, managed and/or stored outside of the planned methods; 2) data is unable to be de-identified; and 3) there is an increase in adverse outcomes including patient falls, missed allied health referrals and/or failed discharges during Phases 2 or 4 (TINSA implementation) when compared to Phases 1 or 3 (baseline). If adverse outcomes are deemed to have occurred because of the study, use of the TINSA will cease, patients will receive usual care, and any serious adverse events will be reported through the hospital procedure channels and to the institutional Human Research Ethics Committee (HREC).

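### Failed discharge depends on a new-episode judgement in an unmasked record audit, so the 30-day readmission comparison is open to attribution that differs by phase

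*Protocol article*

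**What the plan says.** The patient-safety row of Table 1 (protocol article, Outcome measures) has three measures.

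- Readmission: "Failed discharge, defined as unplanned readmission within 30 days not related to a new episode of care".
- Referrals: "Missed allied health referrals (other than those due to a change in condition").
- In-hospital events: "Total number of adverse events during the hospital admission that may be related to allied health input (falls, extension of stroke, aspiration pneumonia, pressure injuries").

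The section headed Retrospective medical record audit gives the source of these data: "A retrospective audit of patient medical records will collect data relating to time-efficiency (e.g., occasions of service), patient safety and adverse outcomes". That audit also records how many TINSA sections were completed. Data management and monitoring says that the Principal Investigator "will be responsible for distribution and collection of surveys, medical record audits, completing the 3-month follow-up phone calls", and also enters all data. Study design states that "neither randomisation nor blinding are feasible". The reason given in the Discussion concerns the treating clinicians, who must know which assessment is in use; it does not address a later reader of the record.

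Readmissions without a relatedness condition do appear elsewhere. The last row of Table 1 has 3-month questions on hospital readmissions, and Scope 3 of the Economic evaluation compares unplanned readmissions between groups.

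**The concern.** The study hypothesis is a time saving with no loss of quality of care, and the abstract says that non-inferiority on patient safety will be explored. Failed discharge is one of the few measures that speak to this after the patient leaves. Whether a return after a stroke or TIA is a new episode is often arguable, and a reader who knows the phase may settle doubtful cases differently before and after the TINSA is introduced. The odds ratio could then move although the number of patients coming back had not. If only the judged count is reported from the audit, nobody can see how much of a difference comes from the exclusions. Failed discharges are also named in the review and stopping rules under Data management and monitoring.

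**Working it through.** **Planned size.** Inputs from Statistical power: difference 20 minutes, SD 25 minutes, significance level 0.05, power 80%. The normal approximation gives n = 2 × (1.96 + 0.84)² × 25² / 20² = 2 × 7.84 × 1.5625 = 24.5, rounded up to 25. The two-sided t-test gives 25.5, rounded up to 26. The stated 26 per group reproduces and is used below as the number per phase. Phases 3 and 4 are limited to 3 months each, so their numbers could differ.

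**Where judgement enters, measure by measure.**

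- Failed discharge: a judgement is needed for each readmission. The audit has no all-cause counterpart. The 3-month readmission questions are asked by phone, with the Principal Investigator calling. In Phases 1 and 2 they go only to patients scoring at least 19/30 on the MoCA, and they cover 3 months from admission, not 30 days.
- Missed referrals: the change-in-condition exclusion has the same form.
- In-hospital adverse events: the bracket names four event types. Read naturally, these are the types chosen as plausibly linked to allied health, and all of them count. The audit section (number of falls) and Scope 2 (counts of adverse events) use plain counts, which supports that reading. The wording does not quite settle it.

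**Counts.** The article gives no readmission rate, so assume a risk of 5% to 20%.

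- Expected events per phase: 26 × 0.05 = 1.3 to 26 × 0.20 = 5.2.
- One reclassified event as a share of the count: 1/1.3 = 77% to 1/5.2 = 19%.

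**Shift with no true difference.** Assume a 15% risk in both phases, every baseline event counted, and a share k of the TINSA-phase events counted. Observed odds ratio = [0.15k / (1 − 0.15k)] / (0.15 / 0.85).

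- k = 0.8: (0.12/0.88) / 0.1765 = 0.1364 / 0.1765 = 0.77.
- k = 0.7: (0.105/0.895) / 0.1765 = 0.1173 / 0.1765 = 0.66.

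**Harm that could be hidden.** Observed risk ratio = true risk ratio × k, so a true ratio of 1/k would look like no difference: 1/0.8 = 1.25 and 1/0.7 = 1.43. At an assumed 10% baseline risk and a true doubling, the chance that the TINSA phase shows more events than baseline is 0.80 with all events counted and 0.63 with k = 0.75 (binomial, 26 per phase). If the baseline phase lost events instead, the shift would run the other way.

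**Price of an all-cause count.** Assume related readmission risks of 5% and 10%, and add 5% unrelated readmissions in other patients in each phase. The odds ratio falls from (0.10/0.90)/(0.05/0.95) = 2.11 to (0.15/0.85)/(0.10/0.90) = 1.59. The risk difference stays at 5 percentage points, but the odds ratio is the planned measure for categorical outcomes.

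**The case against.** Four points on the other side carry weight.

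- A reader might infer that all patient-safety events pass through a relatedness filter. The documents do not support that. The four in-hospital event types most naturally all count, and no case-by-case adjudication is described. Only the ambiguity of the wording remains.
- A reader might infer that no unfiltered count exists. The 3-month readmission and fall data are unfiltered and compared between groups. They do not replace a 30-day audit count, for the reasons given above, but they are a partial check.
- A reader might infer that the Principal Investigator audits alone, or that the comparison is biased. The text says responsible for, not alone, and a second reader or coding criteria could well stand in a fuller protocol. Nothing shows that attribution will differ by phase. The lack of blinding is disclosed.
- Imprecision is the larger limit. At 15% risk each phase has 26 × 0.15 = 3.9 events and 22.1 non-events. The standard error of the log odds ratio is √[2 × (1/3.9 + 1/22.1)] = 0.78, and the 95% interval around 1 runs from about 0.22 to 4.6. Shifts to 0.77 or 0.66 lie well inside it. Power to detect a doubling is only about 0.10, 0.17 and 0.35 at baseline risks of 5%, 10% and 20%, even with perfect attribution.

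The last point lowers the stakes but does not remove the concern. A wide interval does not correct a systematic shift, and with so few events a handful of judgements can decide which way the result points.

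**Conclusion.** The concern holds in a limited form. The article fixes a failed-discharge definition that needs a judgement, and places that judgement in an audit whose responsible person can see the phase. The 30-day readmission comparison is therefore open to attribution that differs by phase, in either direction. The missed-referral exclusion has the same form; the in-hospital adverse events probably do not.

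The size cannot be derived from the documents. The 19% to 77% per event and the odds ratios of 0.77 and 0.66 rest on assumed risks of 5% to 20%, on 26 patients per phase, and on an assumed 20% to 30% of TINSA-phase events being set aside. They show how sensitive the measure is and do not predict a bias. This is a secondary, explored outcome, and the change is a cheap improvement, not a correction on which the study depends.

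**What to change.** From the planned audit, also compare all unplanned readmissions within 30 days whatever their cause, and report this next to the judged failed-discharge count. State in Table 1 that every fall, stroke extension, aspiration pneumonia and pressure injury during the admission is counted without case-by-case judgement of its relation to allied health. Say in advance that if the all-cause and judged comparisons disagree, the safety conclusion will be read with caution.

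The cost is wording in Table 1 and the analysis text, with no extra assessor, because the same records are read. One practical condition applies to both counts: the audit may take place from 2 weeks after discharge, so the readmission item needs a reading late enough to cover the full 30 days. The statistical cost is dilution. Unrelated readmissions pull the odds ratio towards 1, which would favour a claim that quality is unchanged. For that reason the all-cause count should stand beside the judged one and not replace it.

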#### Time of allied health stroke assessments (primary outcome)

Time taken (minutes) by the AHP to complete the initial stroke assessment(s) will be recorded by each AHP involved in the study including the occupational therapist, physiotherapist, and speech pathologist. The AHPs will record “time in” and “time out” when completing a discipline-specific stroke assessment during baseline Phases 1 and 3, or when completing the TINSA during implementation Phases 2 and 4. Total assessment time includes: 1) time taken to read the medical record, 2) time taken to administer the initial patient assessment (excluding interruptions), and 3) time taken to document assessment results in the medical record.

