### Study aim

The primary aim of this research is to understand the benefits (or otherwise) of implementing a novel Transdisciplinary Initial Neurological Screening Assessment (TINSA) on the MHB ASU. We hypothesise that compared to the existing discipline-specific allied health stroke assessments, utilising the TINSA will reduce allied health assessment time by at least 20 minutes during the initial occasion of service, without reducing quality of care. Secondary aims are to evaluate use of AHP time across the participant hospital admission, quality of care provided by AHPs in terms of patient safety and compliance to national stroke guidelines, clinical utility of the novel TINSA, economic implications of implementing the novel TINSA, patient and staff satisfaction, staff interprofessional trust, and staff confidence to complete and share transdisciplinary tasks.

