**Fig. 2 Fig2:**
[figure not shown]
Recruitment timeline for patients and staff

Staff working on the MHB ASU will be provided with a Healthcare Provider Information and Consent Form before agreeing and completing the satisfaction and interprofessional trust surveys (see Additional file 3). The surveys will remain open for 5 business days and returned to a secure slot box or submitted online. Staff will be invited to participate in a focus group at the end of Phase 4. The ASU occupational therapists, physiotherapists, speech pathologists and social workers will be invited to complete a series of online staff confidence surveys before/after completing competency training and at monthly intervals during the implementation Phases 2 and 4. Patients and staff may decline to consent or withdraw their consent to participate at any point and for any reason without prejudice. Upon withdrawal no further data will be collected.

#### Baseline phases 1 and 3

For statistical purposes, the baseline data will be gleaned from Phases 1 and 3 where discipline-specific allied health stroke assessments are utilised within 48 hours for patients admitting to the MHB ASU (i.e., the existing physiotherapy, occupational therapy, and speech pathology stroke assessment).

#### Implementation phases 2 and 4

The novel TINSA (see Additional file 4) replaces discipline-specific allied health stroke assessments and will be utilised within 48 hours of admission to the MHB ASU in Phases 2 and 4. The novel TINSA has been developed in full collaboration with the health professionals on the MHB ASU, including occupational therapy, physiotherapy, speech pathology, social work, nursing staff, and the stroke clinical nurse consultant. The TINSA includes sections on social history, mood, previous level of function, home environment, communication, swallow, respiratory function, vision, cognition, upper limb function, lower limb function, and mobility. Due to the content and clinical skills required, the TINSA can be administered by trained physiotherapists or occupational therapists. The novel TINSA was approved and published in the hospital Policy and Procedure Library prior to use in the study.

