### Statistical analysis

#### Statistical power

The power calculation demonstrates the required participant number per phase to sufficiently power the study to find a minimal clinically important difference in the primary aim. The following time estimates represent the expert opinions of the AHPs working on the MHB ASU. The variation in time taken to complete discipline-specific occupational therapy, physiotherapy and speech pathology initial stroke assessment may range from 80 to 210 minutes total. The smallest clinically important improvement in time taken to allied health stroke assessment would be a decrease of 20 minutes in average total assessment time (i.e., enough time to complete another occasion of service or clinical task). Assuming a similar distribution of patients in each assessment group, a significance level of 0.05, 80% power and a standard deviation of 25 minutes, 26 patients per group will be required to detect a 20-minute difference in total assessment time.

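### The primary outcome totals three disciplines' assessments at baseline but times only the TINSA afterwards, so an initial assessment moved to a follow-on referral counts as time saved

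*Protocol article*

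**What the plan says.** **What is timed.** In the protocol article, under *Time of allied health stroke assessments (primary outcome)*, time "will be recorded by each AHP involved in the study including the occupational therapist, physiotherapist, and speech pathologist". The next sentence fixes the occasions for recording: "when completing a discipline-specific stroke assessment during baseline Phases 1 and 3, or when completing the TINSA during implementation Phases 2 and 4". The total is made up of chart reading, the initial patient assessment and documentation.

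**What the baseline total contains.** *Statistical power* describes it as the three disciplines together: their "initial stroke assessment may range from 80 to 210 minutes total".

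**Who gives the TINSA.** *Implementation phases 2 and 4* says that it replaces the discipline-specific assessments and that "the TINSA can be administered by trained physiotherapists or occupational therapists". The speech pathologist does not give it.

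**What may follow the TINSA.** Table 1 counts stop-and-refer prompts used and referrals identified from the TINSA. Its time-efficiency row also counts referrals to allied health "where no intervention or further assessment is indicated". *Study design* says that "subsequent allied health input will continue as per usual care".

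**The hypothesis.** *Study aim* expects a reduction of at least 20 minutes "during the initial occasion of service". Use of allied health time across the whole admission is a secondary aim.

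**The concern.** The two conditions do not count the same work. At baseline, a speech pathologist's initial assessment is part of the total. In Phases 2 and 4, if the TINSA leads to a speech pathology referral and the speech pathologist then carries out that initial assessment, it is not part of the total. The article nowhere says that such minutes are timed or added. Naming the speech pathologist among those who record time does not help, because recording in Phases 2 and 4 is tied to completing the TINSA.

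The bias can only favour the TINSA. It also bears on the reason given for the 20-minute difference, which *Statistical power* justifies as time freed for another contact or clinical task. If that next contact is the deferred assessment, nothing has been freed. Scope 1 of the economic evaluation uses the same assessment times and would carry the same error.

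This is not a detail that an article can leave to a fuller document, because the article itself fixes which contacts are timed. Minutes that are never recorded cannot be recovered by the later medical record audit.

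**Working it through.** **1. The plan's own figure.** Inputs from *Statistical power*: difference 20 minutes, SD 25, significance level 0.05, power 80%. The normal approximation is n = 2 × (1.960 + 0.842)² × 25² / 20² = 24.5, so 25 per group. The two-sample t-test gives 25.52, so 26 per group, which matches the plan. Power at 26 is 80.7%. A one-sided test would give 20, so the stated figure is two-sided. The sample size arithmetic is sound; the problem lies in what is measured.

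**2. Size of the bias.** Let p be the share of TINSA patients who have one follow-on discipline assessment that would have been in the baseline total, and m its length in minutes. Untimed work per TINSA patient is b = p × m, and net saving = recorded saving − b. The documents give neither p nor m. I assume p from 10% to 75% and m from 20 to 60 minutes.

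**3. Consequences.** The last column is the two-sided t-test probability of a significant result with 26 per group, SD 25 and no true net saving, so that the recorded difference is b alone.

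| p × m | b (min) | Net saving if 20 recorded | Net saving if 103 recorded | Chance of significance at zero net saving |
|---|---|---|---|---|
| 10% × 20 | 2 | 18 | 101 | 6% |
| 25% × 30 | 7.5 | 12.5 | 95.5 | 19% |
| 25% × 45 | 11.25 | 8.75 | 91.75 | 36% |
| 50% × 30 | 15 | 5 | 88 | 56% |
| 50% × 40 | 20 | 0 | 83 | 81% |
| 50% × 45 | 22.5 | −2.5 | 80.5 | 89% |
| 75% × 60 | 45 | −25 | 58 | over 99% |

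**4. Against the pilot.** The Background reports 145 minutes for usual assessment and 42 for the TINSA: 145 − 42 = 103. To bring the net saving below 20 minutes, untimed work would have to average more than 103 − 20 = 83 minutes per patient. That is outside the assumed range.

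**5. Effect of the fix on sample size.** Treat follow-on time as m minutes with probability p, independent of TINSA time. This adds p(1 − p)m² to the variance in the TINSA group, so the averaged variance is [25² + 25² + p(1 − p)m²] / 2.
- 50% × 30: (1250 + 225) / 2 = 737.5, SD 27.2, n = 29.
- 25% × 45: (1250 + 379.7) / 2 = 814.8, SD 28.5, n = 32.
- 50% × 45: (1250 + 506.25) / 2 = 878.1, SD 29.6, n = 35.

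These use the normal approximation and compare with 25 in step 1.

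**The case against.** **The scope is declared.** The hypothesis is confined to the initial occasion of service, the TINSA is stated to replace the discipline assessments, and comparing a replacement with what it replaces is a legitimate question. This stands in part. But the baseline total already spans separate contacts by three disciplines, so the restriction is not applied alike to both conditions, and the 20-minute difference is justified as time freed.

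**Displaced work is tracked.** Table 1 records face-to-face occasions of service by discipline, stop-and-refer prompts, referrals from the TINSA and time to discharge from allied health. Scope 2 covers the whole admission. Large displacement should show up there. This stands as a partial check, but these are counts and intervals, not assessment minutes, and none enters the primary outcome.

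**The mechanism is partly unseen.** What a prompt sets off is in the TINSA form, an additional file not at hand. Follow-on work may be a short targeted check. The Table 1 item on referrals is not confined to TINSA referrals and gives no rate, and later assessments of baseline patients are untimed too. This stands: the bias is only that part of the follow-on work which the baseline total would have included.

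**Stronger readings.** A reader might split the pilot's 145 minutes equally (145 / 3 = 48.3), let half the patients need one such assessment (24.2 minutes), and conclude that the overstatement exceeds the 20-minute threshold and so undoes the result. The documents do not support this. The split and the rate are assumptions, and on the same pilot figures 103 − 24 = 79 minutes remain. A reader might also infer that Phases 3 and 4 are worst affected. That is plausible for patients with aphasia, neglect or cognitive impairment, but the article gives no referral rate by severity.

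**Conclusion.** The asymmetry is in the text, and its direction is towards the TINSA. Its size cannot be derived from the documents. Under the assumed 10% to 75% of patients and 20 to 60 minutes each, the recorded saving is overstated by about 2 to 45 minutes per patient.

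Whether the conclusion is at risk depends on the true saving. Near the pilot's 103 minutes, the finding of a saving holds and only its size is inflated. Near the 20-minute threshold on which the study is powered, the conclusion could be false: an average of 20 untimed minutes gives about an 81% chance of a significant result when the net saving is zero. The documents do not support saying that the TINSA saves no time or that the primary comparison is worthless. The outcome definition should be corrected, but the flaw is not fatal.

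**What to change.** In all four phases, have the occupational therapist, physiotherapist and speech pathologist time every initial assessment by their discipline (chart reading, assessment, documentation) within one common window, for example the 48 hours from admission that the article already uses. Include assessments set off by a TINSA referral. Define the primary outcome as the sum per patient, use that sum in Scope 1, and report TINSA-only time as a secondary outcome.

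The costs are:
- a few more entries on time records that the same staff already keep, and a revised outcome definition;
- a smaller reported saving;
- added variance: under the scenarios in step 5, about 29 to 35 per group instead of 25 by the normal approximation, so power at 26 per group for a 20-minute difference may fall below 80% and should be restated;
- follow-on assessments after the window closes are still missed, so the counts of occasions of service and referrals should be kept as a check.
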